### Statistical analysis

2.12

The data of all participants will be conducted in the final statistical analysis which will be in accordance with the per-protocol principle and the intent-to-treat principle. The data statisticians will be blinded to the group allocation. The SPSS software v19.0 (Statistics 19.0, SPSS, IBM Corp., Chicago, IL) will be used for statistical processing. Measurement data will be presented in the form of mean ± standard deviation, while count data will be expressed as percentage and number. The continuous variables, such as participants’ obesity-related indicators including weight, BMI (weight/height), body fat percentage, basic metabolism value, WC, HC, waist-to-hip ratio (WC/HC), visceral fat area, body fat, and obesity degree will be presented as mean ± SD. Between-group comparisons will be performed by ANOVA or its non-parametric equivalents on changes from baseline to after treatment. Intra-group comparison will be performed by using the Kruskal–Wallis test. All statistical tests will be performed on both sides, and the difference will be considered statistically significant when *P* < .05.

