### Study design

2.1

This trial is designed as a prospective, outcome-assessor-blinded, parallel-arm, single-center (Hubei Provincial Hospital of TCM, China), randomized controlled clinical trial with a 1:1:1 allocation ratio to evaluate the efficacy of herb-partitioned moxibustion plus lifestyle modification treatment for patients with simple obesity. A total of 108 participants, who meet the inclusion and exclusion criteria, will be randomly allocated to heat application group, medicated plaster group, or herb-partitioned moxibustion group (n = 36 each). The patients will receive these treatments once per day, 3 d/wk for 4 weeks. The flow diagram of the study procedure is showed in Figure 1. Participants’ recruiting is from April 2019.

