#### Primary outcomes.

2.8.1

The clinical effectiveness of 4 weeks of

Heat application group,Medicated plaster group, andHerb-partitioned moxibustion group for the improvement of simple obesity will be assessed and determined by the clinical evaluation of nimodipine:

(1)Healing: the clinical symptoms disappear or almost disappear, and the syndrome score is reduced by ≥85%;(2)Significant effect: the clinical symptoms are obviously improved, and the syndrome score is reduced by <85%, but ≥50%;(3)Effective: the clinical symptoms have improved, syndrome scores decreased by <50%, but ≥30%;(4)Invalid: the clinical symptoms were not improved, even worse, and the syndrome score was reduced by <30%.

Integral variation formula (Nimodipine method: [(pre-treatment score-post-treatment score)/pre-treatment score] X100%. This index will be assessed on week 4.

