##### Obesity-Related indicators

2.8.2.1

Weight; BMI (weight/(height); body fat percentage; basic metabolism value; WC; hip circumference(HC); waist-to-hip ratio (WC/HC); Visceral fat area; body fat; and obesity degree will be measured on week 0, 1, 2, 3, and 4.

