#### The IWQOL-Lite scale

2.8.3

The IWQOL-Lite scale will be measured on week 0, 1, 2, 3, and 4. The lower the total score, the lighter the clinical symptoms of the patient.

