#### The syndrome score of TCM

2.8.4

The syndrome score of TCM will be adopted as the criterion of syndrome determination according to the diagnostic and therapeutic evaluation standard of simple obesity revised by the 5th National Obesity Research Conference in 1997. The total score will be then calculated and the unit will be expressed in points. The main clinical symptoms of simple obesity of spleen deficiency and dampness resistance type were divided into 4 levels, which include no (0 point), mild (1 point), medium (2 points) and heavy (3 points). Measurements will be made on week 0, 1, 2, 3, 4.

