### Sample size calculation

2.11

In a previous study, the effective rate of simple obesity in the herb-partitioned moxibustion group was *P*1 = .80. The effective rate of the heat application group was *P*2 = .65, and the effective rate of the medicated plaster group was *P*3 = .6. PASS V.11 software (NCSS, Kaysville, UT) was used to calculate that, based on 80% power to detect a significant difference(α = 0.025, 1 sided), 33 participants will be required for each group. Allowing for a 10% withdrawal rate, we plan to include a total of 108 participants with 36 participants in each group.

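### The continuous secondary outcomes are compared on unadjusted change from baseline, although the week-0 values needed for a more precise baseline-adjusted analysis are collected

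*Protocol article*

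**What the plan says.** The Statistical analysis section (2.12) sets one rule for comparing the arms: "Between-group comparisons will be performed by ANOVA or its non-parametric equivalents on changes from baseline to after treatment". It names no covariate, and no other section mentions ANCOVA or baseline adjustment. The continuous variables listed in that section are the obesity-related indicators. The sentence itself is general, so it also reaches the IWQOL-Lite and TCM syndrome totals, for which no other between-group method is given.

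A week-0 value is scheduled for every one of these outcomes, both in Table 1 and in the outcome sections:

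- Obesity-related indicators: "obesity degree will be measured on week 0, 1, 2, 3, and 4".
- IWQOL-Lite: "The IWQOL-Lite scale will be measured on week 0, 1, 2, 3, and 4".
- TCM syndrome score: "Measurements will be made on week 0, 1, 2, 3, 4".

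The primary outcome is of another kind. It is a four-level response graded by the percentage fall in syndrome score, with the lowest level defined as "Invalid: the clinical symptoms were not improved, even worse, and the syndrome score was reduced by <30"%. The rule on changes therefore applies in practice to the continuous secondary outcomes.

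The design is a "randomized controlled clinical trial with a 1:1:1 allocation ratio", and under Sample size calculation "we plan to include a total of 108 participants with 36 participants in each group".

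**The concern.** Subtracting the week-0 value amounts to assuming that a patient who starts one unit higher will, untreated, finish one unit higher. The true slope of week 4 on week 0 is r × s1/s0, where s0 and s1 are the standard deviations at week 0 and week 4 and r is their correlation. For symptom and quality-of-life scores this slope is commonly below 1. The change score then over-corrects: an arm that happens to start worse tends to show a larger fall through regression to the mean alone.

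Two things are at stake for the secondary outcomes. The standard error is larger than it needs to be, and the estimate from this one trial moves with chance differences at baseline, which are not trivial with 36 per arm. The non-parametric alternative is also applied to changes and shares both features. Since the article states the method outright, this is a choice open to comment and not a detail left to an unseen analysis plan.

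**Working it through.** **Inputs from the protocol article.** 36 per arm, 108 in total, allocation 1:1:1 (Study design; Sample size calculation); two-sided tests at 0.05 (Statistical analysis); week-0 and week-4 values for each outcome (outcome sections, Table 1).

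**Inputs the article does not give.** No standard deviation and no week-0 to week-4 correlation is reported for any outcome, so r is an assumption and is shown over a range. The plan states no precision or power for a continuous outcome, so it has no figure of its own to reproduce here.

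**General comparison.** Per-patient variance entering the contrast between arms:

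- Change score: s0² + s1² − 2·r·s0·s1
- ANCOVA: s1²·(1 − r²)
- Difference: s0² − 2·r·s0·s1 + r²·s1² = (s0 − r·s1)², which is never negative.

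**Equal standard deviations (s0 = s1 = s).** Change score 2s²(1 − r); ANCOVA s²(1 − r²); ratio (1 + r)/2. Estimating the slope costs a factor of about 1 + 1/(3n − 5), which for n = 36 is 1 + 1/103 = 1.0097. The last column is the ANCOVA power for a two-arm contrast, with that factor included, where the change-score test has 80%.

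| Assumed r | Ratio (1+r)/2 | Ratio with small-sample factor | Change-score n per arm matching 36 under ANCOVA, 36/ratio | ANCOVA power |
|---|---|---|---|---|
| 0.3 | 0.65 | 0.656 | 55 | 93% |
| 0.5 | 0.75 | 0.757 | 48 | 90% |
| 0.7 | 0.85 | 0.858 | 42 | 86% |
| 0.8 | 0.90 | 0.909 | 40 | 84% |
| 0.9 | 0.95 | 0.959 | 38 | 82% |
| 0.95 | 0.975 | 0.985 | 37 | 81% |
| 0.98 | 0.99 | 1.000 | 36 | 80% |

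The fourth column uses the large-sample ratio. At r = 0.98 the cost of estimating the slope cancels the gain.

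**Unequal standard deviations.** The ratio can move either way:

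- s1 = 1.25·s0, r = 0.8: s0 − r·s1 = s0 − 1.00·s0 = 0, so there is no gain.
- s1 = 0.7·s0, r = 0.5: change 1 + 0.49 − 0.70 = 0.79; ANCOVA 0.49 × 0.75 = 0.37; ratio 0.47.
- s1 = 0.7·s0, r = 0.7: change 1 + 0.49 − 0.98 = 0.51; ANCOVA 0.49 × 0.51 = 0.25; ratio 0.49.

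These ratios of standard deviations are also assumptions. A narrower week-4 spread is conceivable for the syndrome score, since response is defined by falls of 30% or more on symptoms graded 0 to 3.

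**Chance imbalance.** The standard error of a difference in baseline means between two arms is √(2/36) = 0.24 SD. With equal SDs, an imbalance of that size shifts the change-score contrast by (1 − r) × 0.24 SD, or √((1 − r)/2) of the contrast's own standard error:

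- r = 0.5: 0.5 × 0.24 = 0.12 SD, or √0.25 = 0.5 standard errors.
- r = 0.95: 0.05 × 0.24 = 0.012 SD, or √0.025 = 0.16 standard errors.

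**The case against.** The best defence is that the planned analysis is sound. Under randomisation, ANOVA on changes is unbiased over repeated randomisations and keeps its type I error, and its standard error already allows for chance imbalance. This stands: the point is one of efficiency, not validity.

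The gain is also smallest for some of the outcomes that the Statistical analysis section lists by name. Weight and BMI are likely to correlate very highly over four weeks; at r = 0.95 the variance falls by 2.5% before the small-sample cost and about 1.5% after it. The larger figures belong to assumed correlations of 0.3 to 0.8, plausible for the two scores but documented nowhere, and the simple ratio needs equal standard deviations. This stands too, and is why the size is given as a range.

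A reader might infer more than the documents support, in four ways:

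- That the plan disregards baseline. It does not; it subtracts it. The weakness is that the slope is fixed and not estimated.
- That ANCOVA can never do worse. That is a large-sample result. In a small trial with r near 0.98 the two are level.
- That ANCOVA would make up for a small sample. The statement "based on 80% power to detect a significant difference(α = 0.025, 1 sided), 33 participants will be required for each group" rests on response rates, not on a continuous change, so the calculation is unaffected either way.
- That the primary analysis should be adjusted likewise. ANCOVA does not apply to a four-category response, and the ratio (1 + r)/2 does not carry over to one.

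None of this gives a reason to prefer the change score where the baseline is already in hand.

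**Conclusion.** The point holds as a modest improvement to the analysis of the continuous secondary outcomes. The article fixes an unadjusted change-score comparison although the covariate is available for every such outcome. With equal standard deviations, the reduction in variance runs from 35% at an assumed r of 0.3, through 25% at 0.5 and 10% at 0.8, to practically nothing at 0.98. It is plausibly worth having for the IWQOL-Lite and syndrome scores and negligible for weight or BMI. The direction (no loss in large samples) needs no assumption about r or the standard deviations; the size depends on both, and the documents supply neither.

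**What to change.** Replace the between-group sentence in the Statistical analysis section with wording such as:

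> Week-4 values of each continuous outcome will be compared between arms by ANCOVA, with arm as factor and the week-0 value of the same outcome as covariate. Where the non-parametric route is taken, a rank-based analogue adjusted for the week-0 value will be used.

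Taking the change as the dependent variable is equally acceptable provided the week-0 value is in the model, because the adjusted differences between arms are then identical.

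The cost is one sentence and one residual degree of freedom per model: 108 − 3 − 1 = 104 in place of 108 − 3 = 105 with complete data. No visit, measurement or patient is added.

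### Weekly secondary outcomes are compared between arms only on the baseline-to-end change, so weeks 1–3 go unused and early leavers cannot enter without imputation

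*Protocol article*

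**What the plan says.** Sections 2.8.2.1 to 2.8.4 of the protocol article schedule weekly measurement.

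- Obesity-related indicators: ten are listed, ending with "Visceral fat area; body fat; and obesity degree will be measured on week 0, 1, 2, 3, and 4".
- IWQOL-Lite: "The IWQOL-Lite scale will be measured on week 0, 1, 2, 3, and 4".
- TCM syndrome score: "Measurements will be made on week 0, 1, 2, 3, 4".

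Table 1 shows the same schedule.

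Section 2.12 gives one method for comparing arms: "Between-group comparisons will be performed by ANOVA or its non-parametric equivalents on changes from baseline to after treatment". On the analysis population it says: "The data of all participants will be conducted in the final statistical analysis which will be in accordance with the per-protocol principle and the intent-to-treat". It names no step for a participant without a final value. Section 2.11 plans for loss: "Allowing for a 10% withdrawal rate".

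The primary outcome (2.8.1) is a four-category response based on the percentage fall in the syndrome score. Of its timing the article says: "This index will be assessed on week 4".

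**The concern.** The change from baseline to after treatment is one number per person and outcome. It needs a baseline value and a final value and ignores everything between them. Someone who leaves after week 1, 2 or 3 has no such number, although up to three post-baseline values may be on file. The stated method therefore cannot by itself deliver the stated population.

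Two things are at stake for the secondary results. The first is precision, because information already collected is discarded. The second is possible bias in the week-4 contrast. The article's own dropout criteria (2.4.4) include reluctance to continue, taking drugs that affect weight or appetite, and turning to another way of losing weight. Each could follow a disappointing response. Section 2.6 says participants cannot be masked. Adding a baseline covariate to a week-4 analysis would not solve this, because weeks 1–3 would still be unused.

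**Working it through.** **1. Count.** The indicators in 2.8.2.1 are weight, BMI, body fat percentage, basic metabolism value, WC, HC, WC/HC, visceral fat area, body fat and obesity degree, which makes 10. Adding IWQOL-Lite and the syndrome score gives 10 + 1 + 1 = 12 weekly outcomes. Each has four post-baseline values, of which the stated comparison uses one. No measurement is scheduled after week 4, so I read after treatment as week 4. Section 2.12 lists only the obesity indicators by name just before the ANOVA sentence, but that sentence is general and no other between-group method is given for the two scores.

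**2. Expected loss.** The plan's own figures are 36 per arm, 108 in total and 10% withdrawal. That gives 0.10 × 36 = 3.6 per arm and 0.10 × 108 = 10.8 overall. The remaining 36 − 3.6 = 32.4 per arm is close to the 33 that 2.11 asks for. Whether 33 is itself the right number is a separate question that this point does not use.

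**3. Precision under random loss.** Let p be the fraction lost and R² the share of the variance of the week-4 change explained by the earlier visits. Using those visits for the leavers multiplies the variance of the contrast by about 1 − pR². Assume SD 1 at each visit, correlation 0.8 between adjacent weeks decaying geometrically, and loss after week 2.

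- Variance of the change: 2(1 − 0.8⁴) = 1.181.
- Residual variance given weeks 0–2: 1 − 0.8⁴ = 0.590.
- R² = 1 − 0.590/1.181 = 0.50.
- Variance ratio: 1 − 0.10 × 0.50 = 0.95, a 5% reduction.

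A simulation of 40,000 trials with 36 per arm gave 0.949. A second assumed setting, on a kilogram scale, gave reductions of 5–8%.

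**4. Bias under response-related loss.** The visit structure is as in step 3. The chance of leaving after week 2 depends on the change to week 2. The table gives the week-4 difference among completers in visit-SD units, with attenuation in brackets. The true value is 0.50 (0.503 as simulated in the unequal-loss rows, which is the divisor there).

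| Loss | Weak dependence | Moderate | Strong |
|---|---|---|---|
| 10% overall, one mechanism for all arms | 0.485 (3%) | 0.466 (7%) | 0.456 (9%) |
| 20% overall, one mechanism | 0.476 (5%) | 0.449 (10%) | 0.434 (13%) |
| 5% v 15% by arm | 0.443 (12%) | 0.415 (17%) | not run |
| 3% v 20% by arm | 0.402 (20%) | 0.356 (29%) | not run |

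An analysis using weeks 0–2 for the leavers recovered the true value, to simulation error, in every row. Under the one-mechanism rows at 10%, the arms lose unequal numbers (for moderate dependence, 8.1% v 12.0%) because the real effect leaves more poor responders in the weaker arm.

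**5. Where the bias vanishes.** With no true effect and a common mechanism, the completers' difference was at most 0.003. With equal dropout rates and the same dependence on response relative to each arm's own mean, it was 0.502–0.503 against 0.503. Random loss also left it unbiased.

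**6. Kilogram scale.** In the second setting (slope SD 0.4 kg/week, visit noise SD 0.3–0.8 kg, true difference 1.15 kg), loss of about 8–15% v 4–11% gave bias toward no effect of 0.03–0.11 kg. That is 0.03/1.15 = 3% to 0.11/1.15 = 10%. Loss of 15% v 4% gave 0.17–0.20 kg, or 15–17%. For scale, the variance of the change is (4 × 0.4)² + 2 × 0.3² = 2.74 to (4 × 0.4)² + 2 × 0.8² = 3.84. The standard error with 36 per arm is then √(2 × 2.74/36) = 0.39 to √(2 × 3.84/36) = 0.46 kg.

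**The case against.** A reader might infer that early leavers contribute nothing to the analysis. The article does not say so. It commits to intention to treat on all participants, never restricts the ANOVA to completers, and an imputation rule may stand in a full protocol or SAP that is not shown. That objection stands, so the point is conditional: without imputation, the stated method cannot include them.

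A reader might also infer that the contrast is biased whenever poor responders leave more often. That is too strong, as step 5 of the working shows: the selection must differ between arms. Nor does the article show that poor responders will leave more. It lists reasons for leaving, some unrelated to response, and gives no frequencies.

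Three further objections carry weight. The likely bias is modest, well under half a standard error in the milder kilogram-scale settings, and in every scenario examined it runs toward no effect. The change-score comparison is a legitimate prespecified analysis. The primary outcome is a categorical response and is not analysed by this ANOVA; a repeated-measures model of the secondary outcomes does not settle missing week-4 primary responses.

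It can also be said that 2.12 includes an intra-group comparison that may draw on the weekly values. That is possible, but it does not compare arms.

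The criticism of the method the article does state remains: for every weekly outcome, the between-group comparison passes over three of the four post-baseline values.

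**Conclusion.** The point holds for the secondary continuous and score outcomes, as a cheap and worthwhile improvement rather than a fatal flaw. The loss of precision does not depend on why people leave; its size, 5–8% of variance at 10% random loss, depends on assumed correlations between visits. Bias is conditional on arm-dependent selection. It is about 3–9% attenuation at 10% loss with a common mechanism, more with unequal loss, and about 0 with no true effect. All of these sizes rest on assumed SDs, correlations, effects and dropout mechanisms; the article supplies only the 10% and the arm sizes. The advantage of using the weekly data holds if values are missing at random given what was observed, and is not assured otherwise.

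**What to change.** In 2.12, for the obesity indicators, IWQOL-Lite and the syndrome score, make the main between-group analysis a mixed model for repeated measures on weeks 1–4. Use fixed effects for arm, week, arm × week, baseline value and baseline × week, with an unstructured within-person covariance. Include all randomised participants with at least one post-baseline value. Report the week-4 contrasts between arms with 95% confidence intervals. Keep the change-score ANOVA or rank test as a sensitivity analysis, including for markedly non-normal or ordinal scores.

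The cost is a change of wording and a little more programming, with no new visits or data. The drawbacks are that the model relies on missing at random and still leaves out anyone with no post-baseline value, so it comes closer to the promise to analyse all participants without fully meeting it.

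### Within-group comparisons are assigned to the Kruskal–Wallis test, which treats repeated measurements on the same participants as independent and so gives secondary within-group P values that are too large

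*Protocol article*

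**What the plan says.** Section 2.12 (Statistical analysis) gives two separate instructions. For the arms it says: "Between-group comparisons will be performed by ANOVA or its non-parametric equivalents on changes from baseline to after treatment". For comparisons inside an arm it says: "Intra-group comparison will be performed by using the Kruskal–Wallis test". The same section makes all tests two-sided and applies a 0.05 significance threshold to them.

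Section 2.1 describes a "randomized controlled clinical trial with a 1:1:1 allocation ratio". The measurement schedule is the same for every score and continuous outcome:

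- Obesity-related indicators (2.8.2.1): "body fat; and obesity degree will be measured on week 0, 1, 2, 3, and 4".
- Quality of life (2.8.3): "The IWQOL-Lite scale will be measured on week 0, 1, 2, 3, and 4".
- TCM syndrome score (2.8.4): "Measurements will be made on week 0, 1, 2, 3, 4".

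Table 1 shows the same five time points. The article names no paired or repeated-measures method anywhere.

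**The concern.** Kruskal–Wallis compares the ranks of independent samples. Applied to week 0 against week 4 in one arm, it treats each participant's two values as if they came from two different people. The stable differences between people then stay in the error term, although a paired analysis would remove them. For weight, BMI, waist or body fat over four weeks those differences can be expected to be large relative to the change.

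The consequence is P values without their nominal meaning: the test rejects too rarely when nothing changes, and modest real changes are reported as non-significant. Because 2.12 applies the 0.05 threshold to all tests, these results would be read as significance tests.

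**Working it through.** **Reading the comparison.** The arms are parallel, no subgroups are defined, and each outcome is measured in the same participants at five visits. The only comparison inside an arm that the article supports is across time, so the samples are dependent.

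**Inputs.** From the article: 33 per arm after withdrawals (2.11, "33 participants will be required for each group"), 36 per arm enrolled, and two-sided 0.05. The article states no figure for the within-group analysis, so there is nothing to reproduce. Assumed, because the article gives neither: within-person correlation r of 0.5 to 0.9; true change of 0, 0.3, 0.5 or 0.8 SD; normally distributed data.

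**Why the test is conservative.** For two time points with common variance σ², the variance of the difference in means is 2σ²(1 − r)/n. An independent-samples test assumes 2σ²/n. On ranks the same factor applies with the rank correlation r_s = (6/π)·arcsin(r/2). When nothing changes, the test's z-statistic therefore has standard deviation of about √(1 − r_s) instead of 1, and the actual type I error is about 2[1 − Φ(1.96/√(1 − r_s))].

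- r = 0.5: r_s = 0.483; √0.517 = 0.719; 1.96/0.719 = 2.73; error about 0.6%.
- r = 0.7: r_s = 0.683; √0.317 = 0.563; 1.96/0.563 = 3.48; error about 0.05%.
- r = 0.9: r_s = 0.892; √0.108 = 0.329; 1.96/0.329 = 5.95; error essentially 0.

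**Simulation, two time points.** 10,000 simulated arms per setting; the Monte Carlo margin is at most about 1 percentage point. Each cell gives the percentage rejecting, Kruskal–Wallis / Wilcoxon signed-rank.

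| n | r | no change | 0.3 SD | 0.5 SD | 0.8 SD |
|---|---|---|---|---|---|
| 33 | 0.5 | 0.5 / 4.6 | 14 / 37 | 49 / 78 | 94 / 99 |
| 33 | 0.7 | 0.1 / 4.7 | 10 / 56 | 51 / 94 | 98 / 100 |
| 33 | 0.9 | 0.0 / 4.9 | 4 / 96 | 55 / 100 | 100 / 100 |
| 36 | 0.5 | 0.7 / 5.1 | 16 / 40 | 54 / 81 | 96 / 100 |
| 36 | 0.7 | 0.1 / 4.9 | 11 / 60 | 55 / 96 | 99 / 100 |
| 36 | 0.9 | 0.0 / 4.6 | 5 / 97 | 63 / 100 | 100 / 100 |

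The no-change column agrees with the formula. At r = 0 the two tests coincide (n = 36, 0.3 SD: 22% / 22%), so the gap comes from the ignored correlation.

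**Simulation, five visits.** n = 33, equal correlation between all visits, change growing linearly to 0.3 SD at the last visit, 2,000 runs, Kruskal–Wallis against Friedman. Rejection was 3.7% against 23% at r = 0.5, 0.3% against 56% at r = 0.8, and 0% against 87% at r = 0.9. With no change, Kruskal–Wallis rejected in none of the runs at r = 0.5 or above; Friedman rejected in about 5%.

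**The case against.** **A misplaced test name.** Kruskal–Wallis is the usual rank counterpart of one-way ANOVA for three arms, and the sentence before it mentions non-parametric equivalents. A drafting slip is plausible. It does not rescue the text: an analyst who follows the sentence runs the wrong test, and moving the name to the between-arm sentence leaves the within-group comparison with no method. Nor can an unseen analysis plan excuse it, because the article names a test that does not fit instead of leaving the choice open.

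**Limited consequence.** This stands. The hypothesis (section 1) and the sample size (2.11) concern differences between treatments, and the primary outcome (2.8.1) is a week-4 response category. The primary outcome does use each participant's own percentage reduction in score, but that classifies individuals; it is not a within-group test. A reader might infer that the efficacy conclusion is compromised. The article does not support that, because between-arm comparisons have their own sentence.

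**Conservative direction.** This also stands. A reader might infer a risk of false claims of change; the error works the other way.

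**Dependence on effect size.** A reader might infer that every within-group conclusion will be wrong. The table does not show that: the loss is severe at 0.3 SD, substantial at 0.5 SD and almost gone at 0.8 SD. It would also be too strong to say without qualification that the type I error is 0.1% or less, since it is 0.5–0.7% at r = 0.5.

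**Conclusion.** The sentence is wrong as written, and nothing else in the article corrects it. That the P values are conservative needs only a positive within-person correlation. How conservative depends on assumptions that the article cannot settle. Over r = 0.5 to 0.9 and n = 33 to 36, before-after, Kruskal–Wallis rejects in 0–0.7% instead of 5% when nothing changes. It rejects in about 4–16% against 37–97% for signed-rank at 0.3 SD, about 49–63% against 78–100% at 0.5 SD, and 94–100% against 99–100% at 0.8 SD.

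The affected results are the within-group analyses of the obesity indicators, IWQOL-Lite and the TCM syndrome score. Severity is moderate: it should be corrected before analysis, but it does not threaten the primary outcome or any comparison between arms.

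**What to change.** In 2.12, replace the within-group sentence. Use the paired t-test or the Wilcoxon signed-rank test for week 0 against week 4, and Friedman's test or a repeated-measures model if all five visits are compared. Name Kruskal–Wallis only as the rank alternative to ANOVA between the three arms.

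As a separate recommendation, label within-group results descriptive: lifestyle modification is given to all participants (2.7.1), so change inside an arm cannot isolate the effect of the assigned treatment.

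The cost is one or two sentences. The design, sample size and data collection do not change.
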